## Overview of research plan

We will estimate the effect of antenatal corticosteroid use on child neurodevelopmental outcomes using a novel quasi-experimental design that exploits the clinical cut-off of antenatal corticosteroids administration at 34 weeks. We will link abstracted obstetrical and neonatal chart records from approximately 16,000 preterm births delivered from 2000 to 2013 contained in the British Columbia (BC) Perinatal Data Registry with longer-term child health information contained in BC population-based administrative databases and kindergarten testing data. We will isolate the difference in test scores and adverse child health outcomes occurring at 34 weeks using a regression discontinuity design, while accounting for the general decrease in adverse outcomes associated with advancing gestational age. The study was approved by the Research Ethics Board of the BC Children's & Women's Hospital/University of British Columbia (H18-00620).

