## **Data**

Our study cohort will be created through a linkage of British Columbia's comprehensive population-based databases of detailed obstetrical medical records, medication prescriptions, physician billing, hospital discharge records, vital statistics, and kindergarten child development assessments. The linkage will be performed by PopData BC, a multi-university organization that facilitates the use of the province's databases for research purposes. Maternal and infant personal health numbers and dates of birth will be used as unique identifiers. The linked data are accessed in an anonymized format on a secure server to ensure data confidentiality and security. Follow-up data up to March 31, 2018 will be included, ensuring a minimum of 5 years follow-up for all children.

**BC Perinatal Data Registry:** The BC Perinatal Data Registry contains abstracted obstetrical and neonatal medical records for >99% of deliveries in the province since April 1, 2000. Data quality are maintained through the use of provincially-standardized medical record forms, standardized training of abstractors (certified following a 2-year training program), and regular data checks for plausibility and missing values. Validation studies have established the accuracy and completeness of the database.

**Early childhood development data:** British Columbia has been conducting standardized assessments of child development at kindergarten age since 2001 using the Early Development Instrument, a questionnaire used across Canada and internationally. Data are collected in 3-year waves, so are only available for approximately one-third of children in the province a given year.

**Hospital Discharge Abstract Database:** The BC Hospital Discharge Abstract database contains International Classification of Disease (ICD) codes summarizing the diagnoses and procedures for all discharges, transfers and deaths of inpatients in acute care hospitals in British Columbia. We will only use the first 16 diagnostic coding spots, to ensure that the number of diagnostic coding spots is consistent throughout the study period (a greater number of spots are available in more recent years).

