### Child health outcomes

We will examine adverse outcomes from different points along the spectrum of potential neurodevelopmental consequence, from more subtle differences in lower school development scores to serious adverse neurodevelopmental outcomes such as cerebral palsy. We will also determine if antenatal corticosteroid administration is protective against childhood respiratory conditions.

Our **primary outcome** will be the standardized domain scores of the Early Development Instrument (EDI). The Early Development Instrument was developed by researchers at McMaster University to measure children's development in kindergarten. The EDI provides a holistic assessment of children's development through 104 questions across five domains: physical health and well-being, social competence, emotional maturity, language and cognitive development, and communication skills. The assessments are completed by kindergarten teachers in February for each child in their class, after the teachers have had several months of interaction with the children.

The EDI has been shown to be a reliable and psychometrically-sound tool to measure population-level child development, and is a good predictor of adult health, education and social outcomes. It is used by governments in multiple Canadian provinces (such as Ontario, Manitoba, and British Columbia) and internationally (Australia, Hong Kong) to assess kindergarten readiness and child development. Its widespread use will facilitate the interpretation and comparison of scores from our research.

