For all analyses, infant or child deaths (identified based on vital statistics records) will be assigned the lowest observed score (for EDI scores) or occurrence of the adverse outcome. This will be done to prevent selection bias introduced from differential losses to follow up according to antenatal corticosteroid administration status (i.e., having fewer cases of cerebral palsy in the untreated group because those infants who didn't receive treatment didn't survive infancy to develop the condition).

| Table 1. Study outcome definitions                                               |                                                         |                                                                                                                                                                                                                                                                                           |
|-----------------------------------------------------------------------------------------|---------------------------------------------------------|-------------------------------------------------------------------------------------------------------------------------------------------------------------------------------------------------------------------------------------------------------------------------------------------|
| Outcome                                                                          | Data source                                      | Definition                                                                                                                                                                                                                                                                         |
| Kindergarten age child development scores                                               | Early Development Instrument                            | Mean domains scores for each of:
1. Language and cognitive development
2. Physical well-being
3. Social competence
4. Emotional maturity
5. Communication and general knowledge                                                                                            |

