#### Assessing comparability of groups

We will assess comparability around the 34+0 week cut-off by plotting maternal-fetal characteristics according to gestational age. Specifically, we will examine maternal age, parity, pre-pregnancy BMI, smoking in pregnancy, neighbourhood income quintile, fetal sex, diabetes status, pre-eclampsia status, mode of delivery (Cesarean vs vaginal), type of labour onset (spontaneous vs iatrogenic vs none), placental abruption, and fever in labour/chorioamnionitis. We have no reason to believe these factors will change discontinuously at 34 weeks, but will control for them in our models in the event of meaningful differences.

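### The EDI analysis is protected against selection through death only: no planned check tests whether EDI availability is smooth at 34+0, and the death rule read literally nearly triples the weight of deaths in the EDI set

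*Protocol*

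**What the plan says.** The primary outcome is the set of EDI domain scores, completed by teachers in February of the kindergarten year (Protocol, Child health outcomes). On coverage, the Data section says: "Data are collected in 3-year waves, so are only available for approximately one-third of children in the province a given year". The linked cohort is described as "approximately 16,000 preterm births delivered from 2000 to 2013" (Overview of research plan).

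The rule for loss is in Child health outcomes. It applies to every analysis and reads in part: "infant or child deaths (identified based on vital statistics records) will be assigned the lowest observed score (for EDI scores) or occurrence of the adverse", so a death counts as an event for the binary outcomes. The stated reason is "This will be done to prevent selection bias introduced from differential losses to follow up according to antenatal corticosteroid administration status", and the example that follows is "having fewer cases of cerebral palsy in the untreated group because those infants who didn't receive treatment didn't survive infancy to develop the condition".

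For group comparability the Protocol says: "We will assess comparability around the 34+0 week cut-off by plotting maternal-fetal characteristics according to gestational age". The variables listed there are maternal, obstetric and fetal. The other sensitivity analyses cover outcome definitions, prior admissions and narrower gestational-age windows. Under Exposure measurements, a further sensitivity analysis is promised for missing day-specific gestational age. The Protocol has no rule for survivors without an EDI record and does not list EDI availability among the things to be checked at 34+0.

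**The concern.** A regression discontinuity estimate relies on the children analysed just below and just above the cut-off being exchangeable. The EDI models can use only children who have a score, and having a score is determined about five years after exposure. If the chance of having one jumps at 34+0, and the children lost differ in development from those kept, the EDI jump mixes a treatment effect with a selection effect. Plots of maternal and fetal characteristics in the full cohort would not show this.

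The direction matters in a safety study. If steroid-related difficulty kept some low-scoring children out of the assessment, they would be missing from the treated side and the estimate would move toward no harm. The death rule does nothing about that.

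The death rule also raises a problem of its own. It covers all deaths, while EDI scores exist for only part of the survivors. Deaths and survivors therefore enter the EDI analysis at different sampling fractions.

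**Working it through.** The Protocol states no attrition, mortality or power figure, so there is none to reproduce. Inputs from the Protocol are about 16,000 births, EDI for about one-third, total EDI at the 25th and 50th percentiles of 35 and 41, and a clinically significant difference of 5 points. Mortality, loss rates and the uptake change are assumptions, shown as ranges.

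**1. Children with an EDI record.** 16,000 × 1/3 ≈ 5,333 with and 10,667 without. The Protocol attributes the gap to collection waves. This count therefore describes absence by design and does not measure loss that could bias.

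**2. Weight of deaths under the literal rule.** If all deaths are scored and one-third of survivors are, the share of deaths in the EDI set at mortality m is m / (m + (1 − m)/3).

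- m = 1%: 0.01 / (0.01 + 0.33) = 2.9%
- m = 2%: 0.02 / (0.02 + 0.3267) = 5.8%
- m = 3%: 0.03 / (0.03 + 0.3233) = 8.5%

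The inflation is 2.8- to 2.9-fold. Its effect on the median follows by interpolating between the Protocol's percentiles. With a share w of deaths at the bottom, the pooled median sits at survivor percentile (0.5 − w)/(1 − w), and each 0.25 of percentile is worth 6 points.

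| Mortality | Drop in median, correct weight | Drop in median, literal rule |
|---|---|---|
| 1% | 0.12 | 0.36 |
| 2% | 0.24 | 0.73 |
| 3% | 0.37 | 1.11 |

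Drops that are equal on both sides cancel. What enters the estimated jump is the difference. If mortality were 1% on one side and 2% on the other, deaths would contribute 0.24 − 0.12 = 0.12 points at correct weight and 0.73 − 0.36 = 0.37 under the literal rule.

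**3. Outcome-related loss, with harm and loss on the same scale.** Taking scores as normal, SD = (41 − 35)/0.6745 = 8.9. Let steroid use change by 0.2 to 0.5 at the cut-off (assumed). A 5-point harm per treated child gives a jump of 5 × 0.2 = 1.0 to 5 × 0.5 = 2.5 points. A 5% loss per treated child gives a jump in loss of x = 0.05 × 0.2 = 1.0% to 0.05 × 0.5 = 2.5%. If all of it comes from the lower half, the new median satisfies (F(q) − x)/(1 − x) = 0.5, so F(q) = 0.5 + x/2.

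- x = 1.0%: 8.9 × z(0.505) = 0.11 points; 0.11/1.0 = 11%
- x = 2.5%: 8.9 × z(0.5125) = 0.28 points; 0.28/2.5 = 11%

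**4. What an availability check could show.** Take about 5,333 eligible children, 80% to 90% of them with a record, and 20% to 50% of them below the cut-off (the last two assumed). The two-proportion SE is √[A(1 − A)(1/n₁ + 1/n₂)]. Doubling it is a rough allowance for the discontinuity model. The 95% half-width, 1.96 × 2 × SE, is 3.2 to 4.0 percentage points at A = 0.9 and 4.3 to 5.4 at A = 0.8. The check can reveal a large jump but cannot exclude a small one. Its result should be reported as an interval and not as pass or fail.

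**The case against.** Several points on the other side carry weight.

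- **Missing EDI is mostly by design.** The waves are the only reason the Protocol gives, and a collection calendar has no evident reason to follow gestational age at admission. A reader might infer from the two-thirds gap that the primary analysis is badly selected, or that missing EDI is a far larger biasing loss than death. The documents do not support that, because they give no figure for absence beyond the waves.
- **The sentence on selection bias is narrower than its first half.** The example that follows it concerns deaths only, so part of the defect is wording.
- **No mechanism is documented.** The Protocol says teachers complete the EDI for each child in their class. The file also carries a special-needs flag, so at least some affected children are in it. That impaired children are missed is plausible but assumed. Complete-case analysis of survivors is likewise inferred from silence.
- **A larger effect is easy to produce by mixing scales.** Setting a 5% jump in loss at the cut-off against a harm diluted by uptake looks serious. If steroids caused that loss, it would require 0.05/0.5 = 10% to 0.05/0.2 = 25% of the additionally treated children to disappear.
- **Missing outcomes may be handled in a separate SAP.** That is common. But this document calls itself the pre-analysis plan, lists its pre-specified sensitivity analyses and addresses missing gestational age. The absence of any check on its primary outcome is therefore a fair point.
- **Other outcomes do not depend on EDI.** Cerebral palsy and ADHD come from administrative records and give a partial cross-check.

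These points limit the size of the concern. They do not supply the missing check, and they do not touch the weighting of deaths.

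**Conclusion.** The point holds as a gap in the plan, not as a demonstrated bias. Selection into the EDI analysis is handled for deaths only, and continuity of EDI availability at 34+0 goes unexamined. On consistent assumptions (5% of additionally treated children lost, all from the lower half, uptake change 0.2 to 0.5), the median shifts by 0.11 to 0.28 points. That is about 11% of the matching effect and small against the 5-point clinical threshold.

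The weighting of deaths follows directly from the rule as written and needs only an assumed mortality: 1% becomes 2.9% of the EDI set and 3% becomes 8.5%. It distorts the estimated jump only as far as mortality itself differs at the cut-off. The Introduction cites a reduction in neonatal mortality from treatment, so such a difference cannot be set aside in advance. The concern is confined to outcomes taken from the EDI.

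**What to change.** 1. Define one EDI-eligible denominator: cohort children whose birth year and area of residence fell in an EDI collection wave. This assumes that waves can be identified by area and year, which the Protocol does not spell out. Residence at birth, if the Consolidation file holds it, would fix the denominator at exposure and apply equally to children who died. Apply the death rule only within this denominator.
2. Among eligible survivors, fit the same discontinuity model with presence of an EDI record as the outcome. Report the jump with its 95% interval beside the EDI result.
3. Report an inverse-probability-weighted EDI estimate as a sensitivity analysis, and state that the main analysis of survivors is complete-case.
4. Reword the sentence in Child health outcomes so that it claims to address loss through death only.

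The cost is plan wording and two extra models on files already in the linkage. The main work is building the area-by-year denominator. Weighting corrects only for absence explained by recorded variables, so the availability result should be shown whatever it is.

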## Introduction

Randomized trials have consistently shown that administering antenatal corticosteroids to pregnant women at risk of preterm labour reduces neonatal mortality and respiratory morbidity. As a result, Canadian and international practice guidelines unequivocally advise that all eligible women at 26 to 34 weeks' gestation at risk of an imminent preterm delivery (due to spontaneous onset of labour, preterm premature rupture of membranes, or pregnancy complication indicating an early delivery) should be given antenatal steroids. Antenatal steroids are a *WHO Priority Life-Saving Medicine*, and administration rates are audited as an indicator of perinatal care quality in multiple jurisdictions including Canada.

However, we still lack high quality evidence on the longer-term safety of antenatal corticosteroids. Select studies have signalled that antenatal steroids may have harmful consequences for child neurodevelopment, and obstetrical leaders are beginning to advocate for more restricted use until long-term safety has been convincingly demonstrated. However, generating rigorous evidence on the effects of antenatal steroids for child neurodevelopment is challenging. Follow-up studies of randomized trials were hampered by low follow-up rates and small sample sizes, and observational studies are highly susceptible to confounding. Without high-quality safety evidence, the unproven potential for harm may be causing a treatment with proven neonatal benefits to be withheld unnecessarily.

When randomization is infeasible, regression discontinuity (RD) studies can provide credible causal effect estimates. The design exploits differences in care between individuals immediately on either side of a clinical cut-point as a quasi-randomization tool. With antenatal corticosteroids guidelines recommend administration of corticosteroids up to 33+ 6 weeks' gestation – but not one day later, at 34 weeks+ 0 days, so infants born as little as hours apart have substantially different chances of receiving the treatment. We propose to use this novel design to generate rigorous evidence on the longer-term safety of antenatal steroids. We also propose to examine if antenatal corticosteroid administration's protective effect on respiratory morbidity extends into early childhood.

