## Objectives

To determine if antenatal corticosteroid administration:

- 1) decrease kindergarten child development scores (primary outcome)
- 2) increase risks of adverse neurodevelopmental outcomes such cerebral palsy or attention deficit hyperactivity disorder (ADHD) (secondary outcomes), and
- 3) decrease the risk of lower respiratory tract infection hospital admission under the age of two or childhood asthma (secondary outcomes).

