Each of the five EDI domains are relevant to the detection of adverse neurodevelopmental outcomes. For example, in the physical health domain, questions such as "Can the child manipulate objects?" will capture concerns about fine motor skills and coordination, which are more subtle outcomes on the spectrum to cerebral palsy. Likewise, in the emotional maturity domain, questions such as "Is the child distractable, has trouble sticking to any activity?" assesses characteristics of ADHD. The scores from each domain are standardized into mean scores, and will be examined as continuous variables. We will consider a difference in the total EDI of 5 or greater to be clinically significant. This would reflect a child who scoring 1 point out of 10 lower on each of the 5 subscale domains, and corresponds approximately to the difference between the score of a child on the 50th percentile (41/50) and that of a child on the 25th percentile score (35/50). We will also examine a composite outcome of 'developmentally vulnerable', which is defined as a score <10th percentile on at least two domains (secondary outcome), and an indication of whether the child was identified as having special needs.

Other **secondary neurodevelopmental outcomes** will be cerebral palsy and ADHD, based on previously-published definitions from BC administrative data. Cerebral palsy will be identified using

International Classification of Disease (ICD) codes from hospitalization and physician billing records. ADHD will be identified using prescription records for methylphenidate (Ritalin) and other ADHD medications, based on pediatric ADHD prescribing patterns in Canada described in recent national Canadian Primary Care Sentinel Surveillance Network data. Our **secondary respiratory outcomes** will be a diagnosis of asthma (based on two or more physician billing records or a hospitalization for asthma) and any hospital admission for lower respiratory tract infection during the first two years of life. See Table 1 for detailed outcome definitions.

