| Hospital admission for lower respiratory tract infection in the first two years of life | Hospital discharge records                              | Hospitalization of a child aged 2 or less with any of the following ICD-9 or ICD-10 codes:
466.0 or J20 Acute bronchitis
466.1 or J21 Acute bronchiolitis
480–486 or J12-J18 Pneumonia
487 or J10- J11 Influenza, excluding cases due to certain identified influenza viruses |

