#### Alternative outcome definitions

1. Hospitalization for lower respiratory tract infection in the first two years of age:
  - a) We will model the total number of hospitalizations per child in the first two years after birth rather than the occurrence of any hospitalization. We have opted to use 'any hospitalization' as our primary outcome as it is possible that some subsequent hospitalizations are re-admissions for the same infection rather than new infections.
  - b) We will examine the outcome of RSV bronchiolitis rather than the broader outcome of lower respiratory tract infection (ICD-9 code 466.11; ICD-10 code J21.0).
  - c) We will only include lower respiratory tract infections during the typical RSV season (November to April)
2. Asthma:
  - a) We will examine hospitalization for asthma alone as an outcome (as opposed to a diagnosis using either hospitalization or physician visits)
  - b) We will identify asthma hospitalization in any position of the hospital discharge summary (rather than only in the primary position)
3. Cerebral palsy:
  - a) We will restrict cases of cerebral palsy to those that also have a code for complications including: feeding difficulty/dysphagia; dystonia; spasticity; or developmental delay
  - b) We will restrict analyses to births admitted to hospital prior to May 2011, when a Society of Obstetricians and Gynaecologists of Canada guideline was issued recommending the administration of Magnesium Sulphate for fetal neuroprotection for imminent preterm birth. The guideline recommended administration up to 31+6 weeks, but provided institutional discretion to adopt higher gestational age thresholds (<34 weeks).
4. ADHD:
  - a) We will use define ADHD using physician billing records in addition to N06B prescriptions (ICD-9 code 314.0).

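### Table 1's lower respiratory tract infection outcome does not exclude the birth stay, so listed infection codes given there count as childhood events

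*Protocol*

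**What the plan says.** The outcome is described in several places, and the descriptions do not quite agree.

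- Protocol, Objectives, item 3: the aim is to see whether steroids "decrease the risk of lower respiratory tract infection hospital admission under the age of two or childhood asthma".
- Protocol, Child health outcomes, text: the secondary respiratory outcomes include "any hospital admission for lower respiratory tract infection during the first two years of life".
- Protocol, Child health outcomes, Table 1: the row name again speaks of admission for infection, but the operative definition is "Hospitalization of a child aged 2 or less with any of the following ICD-9 or ICD-10 codes". The list covers acute bronchitis, acute bronchiolitis, influenza and "480–486 or J12-J18 Pneumonia". Respiratory distress is not on it.
- Protocol, Data, Hospital Discharge Abstract Database: the source holds codes "for all discharges, transfers and deaths of inpatients in acute care hospitals in British Columbia", and the first 16 diagnostic positions are used.
- Protocol, Table 1, asthma row: a hospital diagnosis of asthma must be in the primary position. The infection row has no such condition.
- Protocol, Alternative outcome definitions, 1a: "We will model the total number of hospitalizations per child in the first two years after birth". Analysis 1b narrows the outcome to RSV bronchiolitis and 1c to the RSV season.

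No section starts the count at first discharge home or joins transfer records into one episode.

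**The concern.** The Introduction takes it as established that steroids reduce neonatal respiratory morbidity. It then asks whether the "protective effect on respiratory morbidity extends into early childhood". Answering that requires separating what happens in the neonatal stay from what happens later, and the operative rule in Table 1 does not do so. An infant who is never readmitted, but whose birth record carries a listed code in any of the 16 positions, is a case. So is one whose code appears on a transfer record continuing the birth stay.

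The Statistical analysis section attributes any jump at 34+0 weeks to treatment. If steroids change how often listed codes are given in the birth stay, that change becomes part of the jump and would be reported as protection in childhood. Because the fault lies in the outcome definition, covariate adjustment and narrower gestational-age windows cannot remove it. A neonatal benefit would push the estimate towards the protection hypothesised in objective 3. The planned per-protocol estimate divides the jump in outcome by the jump in steroid administration, a quantity below one, and so enlarges any spurious difference.

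**Working it through.** **Stated figure.** There is none to reproduce. The protocol gives no event rate, sample size or power for this outcome.

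**Text check.** Could a birth stay with a secondary pneumonia code fail any condition in the Table 1 row?

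1. Is it a hospitalization? Yes; the source covers all inpatient discharges and transfers, and newborn stays are not set apart.
2. Is the child within the age limit? Yes.
3. Is a listed code present? Yes.
4. Is the code in a qualifying position? No position is required.
5. Is there an exclusion for the birth stay or a continuing transfer? No.

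The stay is therefore an event under the rule, although the infant was not admitted for the infection. Analyses 1a to 1c change the count, the organism or the season. None removes the birth stay, and 1a could count two transfer records of one stay as two hospitalizations.

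**Illustration of size.** All inputs below are assumptions, and the true effect after discharge is set to none (risk ratio 1.00).

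*Simple form.* Let p be the risk of a later event, b the risk of a listed birth-stay code just above the cut-off, and r the intention-to-treat reduction in those codes just below it. Overlap between the two kinds of event is ignored.

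Spurious risk ratio = (p + b(1 − r)) / (p + b)

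- Middle case, p = 6%, b = 1%, r = 20%: (6 + 0.8)/7 = 6.8/7 = 0.97.
- Mildest corner of the grid, p = 8%, b = 0.5%, r = 10%: (8 + 0.45)/8.5 = 0.994.
- Most severe corner, p = 4%, b = 2%, r = 40%: (4 + 1.2)/6 = 0.867.
- Middle p and r with rare codes, b = 0.1%: (6 + 0.08)/6.1 = 0.997.

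*With overlap.* Let q be the later risk, b the birth-stay code risk (taken as independent of q), and k the risk ratio for birth-stay codes.

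Spurious risk ratio = [1 − (1 − q)(1 − bk)] / [1 − (1 − q)(1 − b)]

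For q = 5%:

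| b | k = 0.5 | k = 0.7 | k = 0.9 |
|---|---|---|---|
| 0.1% | 0.991 | 0.994 | 0.998 |
| 0.5% | 0.957 | 0.974 | 0.991 |
| 1% | 0.920 | 0.952 | 0.984 |
| 2% | 0.862 | 0.917 | 0.972 |

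Example, b = 1%, k = 0.5: numerator 1 − 0.95 × 0.995 = 0.05475; denominator 1 − 0.95 × 0.99 = 0.0595; ratio 0.920.

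Over q from 3% to 10%, the full range is 0.80 (q = 3%, b = 2%, k = 0.5) to 0.999 (q = 10%, b = 0.1%, k = 0.9). At b = 0.1% every value lies between 0.984 and 0.999. At b = 0.5% the lowest value is 0.930, and it needs both q = 3% and a halving of the birth-stay codes.

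If birth-stay codes are excluded, the ratio returns to 1.00 in every scenario, by construction.

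**The case against.** The strongest reply has four parts.

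*The code list is narrow.* A reader might infer that the birth hospitalization as such is counted, or that the known neonatal respiratory effect enters the outcome wholesale. The protocol supports neither. A stay counts only if it carries a listed infection code, and respiratory distress is not listed. The benefit cited in the Introduction is on neonatal mortality and respiratory morbidity, with no mention of infection. Contamination needs two further conditions: listed codes must be given in birth stays at a material rate, and steroids must change that rate. The protocol informs neither. This stands, and it limits the point.

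*The wording already says admission for infection.* A sensible programmer might therefore leave the birth stay out. On the other hand, an infection in the birth stay does fall within the first two years of life, so objective 3 read literally could include it. Both readings are possible, which is itself a reason to settle the rule. The operative cell in Table 1 imposes no purpose-of-admission condition, while the asthma row shows that the authors set a position rule where they wanted one.

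*Such rules belong in an analysis plan.* Derivation details often do, and an SAP may exist that is not shown. But Table 1 states a rule that, applied as written, admits events that are not admissions for infection.

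*Partial safeguards exist.* The authors chose any hospitalization over a count because later stays may be readmissions for the same infection, so repeated transfer records affect only analysis 1a. Analysis 1b would not reproduce an effect driven by birth-stay pneumonia codes. That is fair, but 1b still admits RSV bronchiolitis coded during the birth stay, and it answers a narrower question.

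**Conclusion.** The point holds in limited form. As written, Table 1 counts listed infection codes from the birth stay and its continuing transfers, and no planned analysis takes them out. Any steroid effect on those codes would be read as protection in early childhood.

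The size cannot be established from the protocol. On the assumed inputs the spurious risk ratio is about 0.97 in the middle case. It is negligible if birth-stay codes are near 0.1%, and material only at about 1% or more with a strong neonatal effect. Values near 0.80 to 0.87 need several extreme assumptions at once.

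It would go too far to conclude that objective 3 would simply be answered by the neonatal effect already known. In the middle case, 6 of every 7 events above the cut-off are later ones (6%/7%), and the asthma part of the objective is untouched. This is a minor-to-moderate improvement to one secondary outcome.

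**What to change.** In Table 1 and the matching text under Child health outcomes, define the event as a hospitalization that begins after the infant's first discharge home from the birth episode. State that records linked by direct transfer form one episode. Apply the same rule to analyses 1a to 1c. Keep the present definition as a sensitivity analysis, so that the contribution of birth-stay codes can be seen.

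The cost is about one sentence in the protocol and a programming step on admission and discharge dates in the linked hospital records. The plan was written before linkage, so the definition can be settled without sight of the linked outcome results. The downside is that a few genuine infections acquired during the birth stay would no longer count in the main analysis.

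The change does not touch a separate route. Child health outcomes also assigns infant and child deaths the adverse outcome in all analyses, so an effect on neonatal mortality would still enter this outcome.
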